### Statistical Analysis

Statistical analysis will be conducted using SPSS 26.0 statistical software. Count data will involve the ratio of the sex and age variables compared between the 2 groups via the *χ*^2^ test of the 4-fold table or the Fisher test. The SF-MPQ scores, PPTs, and ODI scores are the rank data. Therefore, the Mann-Whitney *U* test will be used for the intergroup comparison, and the Wilcoxon symbolic test will be applied for the intragroup comparison. Paired 2-sided *t* test will be used to assess the difference in ALFF and ReHo between the 2 groups. In addition, Pearson correlation coefficients will be used to estimate the connection between the seed region and all of the voxels within the whole brain separately based on the patients. Statistical significance will be set at *P*<.05 (2-sided).

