### Inclusion Criteria

The inclusion criteria for the participants are as follows: (1) right-handed; (2) age between 18 and 60 years; (3) computed tomography or magnetic resonance imaging examination show L4-L5 or L5-S1 disc herniation; (4) the main manifestation is nerve root pain, and the imaging is consistent with the nerve localization; (5) the neuropathic pain rating scale (Douleur Neuropathique 4 questions) score is ≥4; (6) patients who did not take painkillers or nutritional neurodrugs for nearly 1 month and did not receive systematic treatment; and (7) patients who voluntarily want to participate in clinical trials and sign informed consent forms.

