### Outcome Measurements

We will present the trial results by using both objective and subjective indicators. fMRI will be used for the main measurements, reflecting the changes in the participants’ brain structure and functional changes. Short-Form McGill Pain Questionnaire (SF-MPQ), pressure pain thresholds (PPTs), and the Oswestry disability index (ODI) will indicate the degree of pain and lumbar dysfunction and will be used for secondary outcome measurements.

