#### Safety Evaluation

The investigators will assess the adverse events, defined as unexpected or adverse reactions occurring during or after treatment. In this experiment, adverse events [26] will be defined as (1) syncope, (2) ecchymosis, (3) increased pain, (4) fracture, and (5) skin allergy. The investigator will assess and solve the adverse events during the study, reporting them to the appropriate departments and ethics committees. Following that, they will monitor all the adverse events until the event resolves or the participant’s condition becomes chronic or stable, and they will make every effort to ensure their safety and record the relevant information in case report forms.

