#### Follow-Up

To evaluate the efficacy and safety of the intervention, we will follow up with the participants for 1 month after the end of the treatment. A month after the treatment ends, the results evaluator will call the participants to investigate the recurrence of their symptoms. Participants can also inform evaluators of their clinical symptoms face-to-face or via email, text message, or WeChat at the relevant timepoint.

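### Age in years is classed as count data and assigned a four-fold-table test with no cutpoint; the effect is confined to the baseline comparison

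*Protocol article*

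**What the plan says.** The Statistical Analysis section of the protocol article puts age and sex together under one data type: "Count data will involve the ratio of the sex and age variables compared between the 2 groups". The method for both is the chi-square "test of the 4-fold table or the Fisher test". No age cutpoint or age bands are given there or elsewhere in the article.

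Under Inclusion Criteria, age is given in years: "age between 18 and 60 years".

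For the main outcome, Outcome Measurements states that "fMRI will be used for the main measurements, reflecting the changes in the participants’ brain structure and functional changes". Statistical Analysis then names a paired two-sided t test which "will be used to assess the difference in ALFF and ReHo between the 2 groups". No covariate is named.

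**The concern.** Age in years is a measurement. Sex is a two-category variable and belongs in a four-fold table; age does not until someone divides it. Because the article does not say where, the age comparison cannot be run as written. The analyst must pick a split, possibly after seeing the data, and different splits of the same ages can give different P values.

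What is at stake is modest. The age comparison describes the arms at baseline, and nothing in the article makes any later analysis depend on its result. A related opportunity is also missed: age and sex will be known for every participant, yet neither is named in the comparison of the main fMRI measures, where they might improve precision.

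**Working it through.** The article gives no figure on this point to reproduce, so the check is mainly a reading of the text, followed by one short calculation for the optional covariates.

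**1. Does the test fit the variable?**

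| Item | Sex | Age |
|---|---|---|
| Scale in the article | two categories | years, 18 to 60 |
| Label in Statistical Analysis | count data | count data |
| Can enter a four-fold table directly | yes | no, needs a cutpoint |
| Cutpoint given | not needed | none |

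Fisher's test does not remove the problem. It can be extended to more than two categories, but age would still have to be banded and no bands are given.

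**2. What a cut does.** Take the midpoint of the eligible range purely as an illustration: (18 + 60)/2 = 39 years. Patients aged 18 and 38 then fall in the same cell although 20 years apart, while patients aged 38 and 40 fall in different cells although 2 years apart. The sample median, or either end of the 30-50 age band mentioned in the Introduction, would be as easy to defend as 39. The article does not choose between them.

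**3. How far the effect reaches.** Statistical Analysis names separate tests for SF-MPQ, PPT, ODI, ALFF and ReHo. None is conditional on the age comparison, so the effect stops at the baseline description.

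**4. The sentence on ALFF and ReHo.** A paired t test needs two values from the same person or a matched pair. Trial Design describes two parallel arms of different patients, randomised 1:1, so a comparison between the groups is not paired. The sentence needs rewriting for that reason alone, which makes it the natural place to name covariates.

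**5. What the covariates could be worth.** If covariates explain a share R² of the outcome variance, adjustment reduces the residual variance by the factor (1 - R²). The equivalent gain in sample size is 1/(1 - R²) - 1.

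- R² = 0.05 (assumed): 1/0.95 - 1 = 0.053, about 5%.
- R² = 0.15 (assumed): 1/0.85 - 1 = 0.176, about 18%.

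With the 76 participants stated in Trial Design, that is 76 × 0.053 = 4 to 76 × 0.176 = 13 additional participants. The cost is two degrees of freedom: residual degrees of freedom fall from 76 - 2 = 74 to 72, or from 60 - 2 = 58 to 56 if 30 per arm are evaluable. The 5-18% is before deducting the small loss from estimating two coefficients. The article gives no value of R².

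**The case against.** The strongest reply is that this is a wording slip in a baseline table. Randomisation, not a baseline test, makes the arms comparable, so a poor test of age harms no treatment comparison. That stands, and it sets the size of the point. It does not remove the point, because the article states a method for age and that method does not fit.

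A second reply is that covariate adjustment is a matter of choice and is commonly left to a statistical analysis plan, which is not shown here. That also stands. The covariates are offered as an improvement and not as the correction of an error.

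Three stronger readings are tempting, and the documents do not support them.

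- **That the four-fold test would let a real age imbalance pass unnoticed.** A split does lose information. In simulation with 38 per arm, normally distributed ages, a true shift of 0.5 SD and a median split, a t test detects the shift 58% of the time and the four-fold chi-square about 36%. But randomisation rules out a true shift between the arms, a baseline significance test has no useful job in a randomised trial, and no analysis depends on its result. Lost power in that test is not a measure of harm.
- **That leaving out age and sex inflates the false-positive rate of the fMRI comparison.** Over all randomisations, a properly specified unadjusted comparison keeps its 5% error rate. An excess appears only after conditioning on a particular imbalance and assuming a correlation between age and the fMRI measure. The article gives no such correlation, and one with the level of brain activity need not carry over to its change.
- **That adverse events and 1-month recurrence have been wrongly left out of the count analysis.** The article lists adverse events ("1) syncope, (2) ecchymosis, (3) increased pain, (4) fracture, and (5) skin allergy") and says the evaluator "will call the participants to investigate the recurrence of their symptoms". The sentence on count data does not say it is limited to sex and age, recurrence is not defined as a yes/no outcome, and an article may leave such analyses to the full plan.

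**Conclusion.** The point holds as a minor error of stated method. Age, recorded in years, is labelled count data and assigned a test that needs a dichotomy the article does not define. That conclusion rests on the text alone and needs no assumption. Its effect is confined to the baseline comparison.

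Adding age and sex to the between-arm ALFF and ReHo comparison is a worthwhile, nearly free improvement. Its value, about 5-18% more participants, depends wholly on the assumption that the two variables explain 5-15% of the variance. If they explain little of the before-to-after change, the gain is close to nil. The absence of covariates is not an error, and the unadjusted comparison of independent groups would be valid.

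**What to change.** In the Statistical Analysis section:

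1. Summarise age by arm as mean (SD) or median (IQR), and sex as count and percentage. Remove age from the sentence on count data, and do not use a test of dichotomised age as a balance check.
2. As an improvement, replace the paired t test for the between-arm comparison of ALFF and ReHo with an independent-groups model that includes age (as a continuous variable) and sex as covariates. Fix them before the data are analysed.

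The first change is wording only. The second costs two model degrees of freedom. Neither needs a new data item: age is needed for eligibility, and sex is already to be compared between the arms. The Abstract reports that data were still being collected and that no analysis had been performed, so at that stage both changes could be made without knowledge of the results.

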#### PPT Test

PPT is a quantitative sensory test that can effectively describe the intensity of pain [24]. When the patient lies in the prone position, the estimator first locates the Dachangshu (BL25), Guanyuanshu (BL26), and Xiaochangshu (BL27) on the patient’s erector spinae muscles and Zhibian (BL54) and Huantiao (GB30) on the gluteus maximus muscles and uses them as test points (Figure 4). Then, the estimator will use the handheld tenderness tester (FTX50, Wagner) to press the test points at a uniform speed, lock it immediately when the patient feels pain, and then record the pressure value. The PPT will be measured every 5 minutes; a total of 3 measurements will be recorded, and the average will be taken to indicate the PPTs.

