#### ODI Questionnaire

The ODI is a commonly used questionnaire for self-quantification of dysfunction in patients with LDH, and it has good reliability and sensitivity in patients with LDH [25]. This questionnaire consists of 10 questions. The score for each question ranges from 0 to 5. The maximum total score is 45 points. ODI score = [actual score/(5×number of actual answered questions)]×100%. The higher the score, the more severe the dysfunction.

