### Sample Size Calculation

There is still no consensus on sample size estimates for fMRI studies. Desmond and Glover’s [31] empirical research results indicate that to achieve 80% test power at the single voxel level in magnetic resonance imaging data with a multiple comparison correction threshold of 0.05, at least 24 participants are required. We also referred to similar studies investigating neuroimaging mechanisms related to LDH and combined them with the research design for this topic [12,18]. The visual analog scale was selected as an important indicator of LDH pain level [32]. According to literature [33], patients with LDH had a score of 4.28 (SD 1.16) points after Tuina intervention and a score of 5.68 (SD 1.26) points after traction intervention. We used G*Power 3.1 software to calculate the sample size based on the mean, wherein α is .05 and power is .85. Each of the 2 groups require 30 cases. With 20% dropout, 38 cases are required for each group for a total of 72 cases.

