## Discussion

### Overview

This randomized controlled trial investigates the clinical efficacy and potential mechanism of Tuina in treating LDH. The results of this trial will be helpful in clarifying the cerebral mechanism of Tuina in the treatment of LDH. LDH occurs when the annulus fibrosus of the lumbar intervertebral disc tears, the nucleus pulposus herniates, and the dural sac and nerve root are stimulated and compressed [1]. This causes a wide range of symptoms, including low back pain, radiation pain in the lower limbs, and numbness. Pain, the primary symptom of LDH, is usually the main reason for patients to seek medical treatment [34].

Tuina is a traditional Chinese medicine treatment method based on meridian acupoint theory and modern anatomy [35]. A therapist manipulates the patient’s skin, muscles, and bones with both hands, including pressing, kneading, pushing, pulling, and shaking. Tuina is widely used for the treatment of LDH in China because of its proved effectiveness in relieving pain and muscle tension and improving dysfunction [35,36]. Traction is a technique used for stretching soft tissue and separating joint surfaces or bones to achieve the treatment goal [37]. Through electrodes placed on the skin, TENS creates pulsed alternating current. This can help relieve pain by activating the central nervous system’s endogenous inhibition mechanism [38-40]. The *Chinese Journal of Evidence-Based Medicine* published the “Evidence-based practice guide for nonoperative treatment of LDH” in 2024, listing Tuina, traction, and TENS as routine treatments and interventions for LDH [41].

Pain is considered to be an unpleasant and emotional feeling related to actual or potential histopathology [42]; therefore, changes in pain perception should include subjective and objective indicators. This study will use subjective SF-MPQ and ODI scores to assess changes in pain perception and dysfunction, while the objective index of tenderness threshold will demonstrate changes in pain symptoms. The combination of subjective and objective indicators can comprehensively reflect the changes in the symptoms of patients with LDH, reducing the occurrence of potential bias and improving the quality of clinical evidence.

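### The rank-data label used to justify an unadjusted Mann-Whitney test does not fit PPT, ODI or VAS; ANCOVA on baseline would be more efficient for these secondary outcomes

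*Protocol article*

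**What the plan says.** The Statistical Analysis section groups all three clinical instruments together and derives the test from that label: "The SF-MPQ scores, PPTs, and ODI scores are the rank data. Therefore, the Mann-Whitney *U* test will be used for the intergroup comparison". For change within each arm, "the Wilcoxon symbolic test will be applied for the intragroup comparison". The section names no covariate and does not say whether post-treatment values or changes enter the between-group test.

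Elsewhere the article describes the same measures as follows:

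- **PPT Test:** "a total of 3 measurements will be recorded, and the average will be taken to indicate the PPTs".
- **ODI Questionnaire:** "ODI score = [actual score/(5×number of actual answered questions)]×100", expressed as a percentage.
- **SF-MPQ Indicators:** a 0 to 10 VAS, summed pain rating indices, and a present pain index with six ordered levels.
- **Sample Size Calculation:** G*Power was used to "calculate the sample size based on the mean", with VAS 4.28 (SD 1.16) after Tuina and 5.68 (SD 1.26) after traction.
- **Discussion, Overview:** "This study will use subjective SF-MPQ and ODI scores to assess changes in pain perception and dysfunction".

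Outcome Measurements makes fMRI the main measurement and these scores secondary.

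**The concern.** The choice of test is derived from a statement about the data that the rest of the article contradicts. An averaged pressure reading is a continuous physical quantity. A percentage score and a 0 to 10 scale are usually analysed as quasi-continuous, and the article itself treats the VAS that way when it sizes the trial. Of the measures listed, only the six-level present pain index is plainly ordinal.

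The consequence is that the between-group test has no place for a baseline covariate, although a paired within-group test needs baseline values. Randomization describes random sequence numbers and no stratification on severity, so the design does not use baseline pain either. The article's Objective and Conclusions promise a comparison of Tuina with TENS plus traction, and these scores carry the clinical side of it. What is at stake is precision, and a result expressed in points, for those secondary comparisons.

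**Working it through.** **1. The article's own sample size.** Inputs from Sample Size Calculation: means 4.28 and 5.68, SDs 1.16 and 1.26, alpha 0.05, power 0.85. Statistical Analysis sets two-sided testing.

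- Pooled SD = √((1.16² + 1.26²)/2) = √1.4666 = 1.211.
- Difference = 5.68 − 4.28 = 1.40, so d = 1.40/1.211 = 1.156.
- Two-sided n per group for 85% power: 14 (normal approximation) or 15 (t test).

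The stated 30 per group is not reproduced; it equals the two-group total, 2 × 15. Allowing for 20% dropout, 30/0.8 = 37.5, rounded up to 38, is right, but 2 × 38 = 76, not the 72 printed there. Those are separate matters. Here they show only that 30 analysed per arm is generous for the assumed VAS effect.

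**2. Cost of the rank test alone.** Under normality the Mann-Whitney test has efficiency 0.955 relative to the t test. With 30 per arm, the effect that a t test detects with 85% power is d = 0.787 (0.787 × 1.211 = 0.95 VAS points). Mann-Whitney power there is 83.3%, so the rank test by itself costs little.

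**3. Cost of leaving baseline out.** Let r be the baseline-outcome correlation. The article gives none, so 0.3, 0.5 and 0.7 are assumed. In units of the outcome variance, and with equal variance at baseline and follow-up:

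| Analysis | Variance | r=0.3 | r=0.5 | r=0.7 |
|---|---|---|---|---|
| Post values | 1 | 1.00 | 1.00 | 1.00 |
| Change | 2(1−r) | 1.40 | 1.00 | 0.60 |
| ANCOVA | 1−r² | 0.91 | 0.75 | 0.51 |

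The ratio of change to ANCOVA variance is 2/(1+r), which exceeds 1 for every r below 1. ANCOVA is therefore more efficient under either reading of the text. Against Mann-Whitney on post values, ANCOVA needs 1 − 0.955(1−r²) fewer patients: 13%, 28% and 51%.

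**4. Power.** Simulation: 30 per arm, normal data with SD 1.211, two-sided 0.05, 4000 runs per setting, so the Monte Carlo standard error is at most √(0.25/4000) = 0.8 points. Results are in percent for r = 0.3/0.5/0.7.

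| Effect | Mann-Whitney, post | Mann-Whitney, change | ANCOVA |
|---|---|---|---|
| d = 1.16 (article's VAS effect) | 99.1/99.1/99.2 | 95.5/99.0/100.0 | 99.5/99.9/100.0 |
| d = 0.79 (assumed) | 83.1/83.5/81.9 | 69.3/82.9/96.9 | 88.3/93.0/98.7 |
| d = 0.5 (assumed) | 46.0/44.9/45.4 | 34.5/45.2/65.6 | 50.2/59.9/74.9 |

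On post values the true Mann-Whitney power does not depend on r; the spread within each cell is simulation noise. Taking 83% and 45% as the common values, the gain from ANCOVA is about 5/10/16 points at d = 0.79 and about 5/15/30 points at d = 0.5. At the article's own effect it is below 1 point. If changes were compared there instead, the gap would reach 4 points at r = 0.3 (95.5 against 99.5).

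**The case against.** Mann-Whitney does not require ordinal data. It is a valid test for continuous, skewed or bounded scores, randomisation protects the type I error without adjustment, and chance imbalance is already allowed for in the P value. The label also has some basis, since SF-MPQ items are graded none to severe and ODI sums items scored 0 to 5. All of this stands: the wrong label does not make the test wrong.

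A reader might infer three stronger points, and the document supports none of them as fact.

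- **That the plan ignores baseline.** The section does not say whether post values or changes are compared, and the Overview speaks of assessing changes. If changes are used, baseline enters, though less efficiently than by ANCOVA.
- **That power is seriously damaged.** At the article's own VAS effect the loss on post values is under 1 point. Larger losses need a smaller effect and an assumed correlation, and the simulation's normal data favour ANCOVA.
- **That no treatment effect can be reported.** None is named, but a Hodges-Lehmann shift with a confidence interval could accompany the test, and an analysis plan that is not shown may provide it.

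Smaller effects are still worth considering. The assumed VAS difference is against an arm described as traction, whereas this trial's control adds TENS, and PPT and ODI have no sizing of their own.

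**Conclusion.** The point holds as one of rationale and efficiency. The rank-data label is wrong for PPT, does not suit the ODI percentage or the 0 to 10 VAS, and is inconsistent with sizing on VAS means and SDs. The test it leads to is valid but cannot use baseline as a covariate, so it is less efficient than ANCOVA on either reading.

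The size depends on two quantities that the article does not give for this purpose: the baseline-outcome correlation and a realistic effect on each score. Over r from 0.3 to 0.7, with 30 per arm and normal data, the gain over Mann-Whitney on post values runs from about 5 to 16 points of power at d = 0.79 and from about 5 to 30 points at d = 0.5; it is negligible at d = 1.16. Because the outcomes are secondary and type I error is intact, this is a worthwhile, low-cost improvement and not a threat to the trial's validity.

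**What to change.** Remove the rank-data rationale and replace the between-group sentence for these secondary outcomes with:

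> VAS, pain rating indices, PPT and ODI at the planned end-of-treatment assessment will each be compared between groups by ANCOVA with the participant's own baseline value as covariate, reporting the adjusted mean difference with 95% CI. A rank-based analysis will be the sensitivity analysis and the main method for the six-level present pain index. Within-group tests are descriptive.

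The time point is tied to the planned assessment and not to a named day, because the assessment schedule is in a figure that is not shown. The rank-based analysis should also state whether it uses post-treatment values or changes.

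Cost: wording only. ANCOVA is available in the SPSS software already named, no new data are needed, and the article reports that no analysis had been done, so the change can be dated and recorded before the data are analysed. The one downside is that residuals must be checked; the rank-based analysis is the back-up if they look poor.

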**Objective:**

Our randomized controlled parallel-group trial aims to compare the effects of Tuina with those of transcutaneous electrical nerve stimulation (TENS) with traction in patients with LDH.

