## Methods

### Trial Design

This is a single-center randomized controlled trial with 2 parallel arms: the Tuina intervention group and traction with transcutaneous electrical nerve stimulation (TENS) intervention group. A total of 76 eligible patients with LDH will be recruited for this trial, and patients with LDH will be randomly assigned to the groups in 1:1 ratio. All patients will provide written informed consent. Outcome evaluation and statistical analysis will be performed by 2 researchers who do not know the specific groups. The trial design flowchart is shown in Figure 1, and the study schedule is shown in Figure 2. This study will be conducted in the Rehabilitation Hospital affiliated to Fujian University of Traditional Chinese Medicine. This study follows the CONSORT (Consolidated Standards of Reporting Trials) guidelines (Multimedia Appendix 1).

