### Randomization

An independent technician will use the SPSS statistical software (version 26.0; IBM Corp) to generate random sequence numbers, and participants will be randomly divided into the Tuina intervention group or the traction with TENS intervention group in 1:1 ratio. Random sequence numbers will be sealed in opaque envelopes. The envelopes will be opened in a numerical order to determine the allocation for the participants.

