### Primary Outcome Measurement

The fMRI examination will be performed in the Imaging Department of the Rehabilitation Hospital affiliated to Fujian University of Traditional Chinese Medicine. The first fMRI scan will be performed 1 day before the start of treatment, and the second fMRI scan will be performed within 6 hours after the last intervention. The fMRI data will be collected by a 3.0 Tesla magnetic resonance scanner (MAGNETOM Prisma 3.0T, Siemens) with 64-channel phase-array head coils. During the acquisition process, participants will be required to close their eyes, relax, stay awake, keep their heads fixed as far as possible, and not perform thinking activities. We will perform fMRI at the beginning and end of the experiment.

To acquire the structural images, we will use the following parameters. The T1-weighted imaging scan parameters are as follows: time of repeat=2200 ms, time of echo=2.48 ms, flip angle=8°, field of view=230 mm×230 mm, matrix=256×256, resolution=0.98×0.98×1 mm^3^, slice number=160, and slice thickness=1.0 mm. The functional images will be acquired using the following parameters: time of repeat=2000 ms, time of echo=30 ms, flip angle=90°, field of view=230 mm, matrix=64×64, resolution=3.6×3.6×3.6 mm^3^, slice number=37, slice thickness=3.6 mm, and scan time=10 minutes for 300 timepoints.

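### The only group test named for the primary ALFF and ReHo outcomes is a paired t test, which does not fit two independent, unmatched arms

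*Protocol article*

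**What the plan says.** All statements are from the protocol article.

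- **Design.** Trial Design: "This is a single-center randomized controlled trial with 2 parallel arms". Randomization: "participants will be randomly divided into the Tuina intervention group or the traction with TENS intervention group in 1:1 ratio". Neither section mentions matching, paired allocation or crossover.
- **Aim.** The Objective in the abstract says the trial "aims to compare the effects of Tuina with those of transcutaneous electrical nerve stimulation (TENS) with traction in patients with LDH".
- **Primary outcome.** Outcome Measurements: "fMRI will be used for the main measurements, reflecting the changes in the participants’ brain structure and functional changes". Under Primary Outcome Measurement each patient is scanned twice, one day before treatment starts and again at the end: "the second fMRI scan will be performed within 6 hours after the last intervention".
- **Test for ALFF and ReHo.** Statistical Analysis: "Paired 2-sided *t* test will be used to assess the difference in ALFF and ReHo between the 2 groups".
- **Tests for the secondary outcomes.** The same paragraph says "the Mann-Whitney *U* test will be used for the intergroup comparison, and the Wilcoxon symbolic test will be applied for the intragroup comparison". Chi-square or Fisher tests compare sex and age between the groups.
- **Other imaging statistic.** "Pearson correlation coefficients will be used to estimate the connection between the seed region and all of the voxels within the whole brain". This builds each patient's connectivity map; it is not described as a comparison of groups.
- **Software.** Statistical Analysis names SPSS 26.0. The sections on fMRI data preprocessing and ALFF analysis name the SPM-based CONN toolbox and AFNI.

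**The concern.** A paired t test needs a rule that links each observation in one set to exactly one observation in the other. Here the only natural links are between a patient's own two scans. The sentence instead attaches the paired test to the difference between the arms, which contain different people.

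This is the only group test that the article names for any primary measure, and the aim is a comparison of arms. If the sentence were followed, a claim that Tuina alters brain activity differently from TENS with traction would rest on an undefined test or on no between-arm test at all. The error also carries forward: under FC Analysis, connectivity is calculated from regions that the ALFF or ReHo analysis shows to differ, so the choice of those regions depends on the same test.

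**Working it through.** The plan gives no figure of its own for this test, and no effect size for ALFF or ReHo. The check therefore takes the possible readings in turn.

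**Inputs.** Per-arm size before dropout 30, dropout 20%, per-arm size 38 (Sample Size Calculation). The last figure reproduces: 30/(1 − 0.20) = 37.5, rounded up to 38. Two arms of 38 give the 76 stated under Trial Design. Alpha is 0.05 two-sided (Statistical Analysis). Standardised differences d of 0.5 and 0.8 are assumptions.

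**Reading 1: pairs formed across arms.** The statistic is t = D/(s_d/√n), with

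- D = mean(Tuina) − mean(TENS with traction), which is the same for every pairing;
- s_d² = s_T² + s_C² − 2·r·s_T·s_C, where r is the correlation across the pairs.

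With no real pairs, r reflects only the order in which patients happen to be listed, so t and its p-value change with that order.

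The test also needs equal numbers. Suppose each of the 38 patients per arm completes independently with probability 0.80:

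P(equal completers) = Σ_k [C(38,k)·0.8^k·0.2^(38−k)]² = 0.114.

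As a rough check, the SD of completers per arm is √(38 × 0.8 × 0.2) = 2.47, and 1/(2·√π·2.47) ≈ 0.114. So in roughly nine trials out of ten some patients would have to be left out to form pairs.

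The cost when numbers are equal, at n = 30 per arm:

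| Quantity | Independent test | Arbitrary pairing |
|---|---|---|
| Degrees of freedom | 2 × 30 − 2 = 58 | 30 − 1 = 29 |
| Critical t, 5% two-sided | 2.002 | 2.045 |
| Power at d = 0.8 (assumed) | 0.861 | 0.850 |
| Power at d = 0.5 (assumed) | 0.478 | 0.465 |
| Simulated type I error (100,000 null trials) | 0.051 | 0.050 |

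The power loss is 0.011 and 0.013, and type I error holds.

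**Reading 2: pre-post pairs within each arm.** Let δ_T and δ_C be the mean changes in the two arms. The paired tests address δ_T = 0 and δ_C = 0. The trial's question is δ_T − δ_C = 0. Neither within-arm result, nor the two together, tests that.

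**Reading 3: a slip for two-sample.** The test would then fit the design, but the published text names a different one. It would also remain open whether post-treatment or change maps are compared.

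**The case against.** The strongest reply is that *paired* is a one-word slip. The sentence's stated purpose is a between-group difference, and the sentence before it assigns separate tests to between-group and within-group comparisons of the secondary outcomes. This is plausible, and it limits the finding: the plan lacks a valid test as written, not necessarily in intention. The text still needs correcting. Nor does the condensed format or an unseen analysis plan excuse it, because the article does not leave the test open; it names one that does not fit.

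Four stronger readings are tempting, and the documents do not support them.

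- **Inflated false positives or a serious loss of power.** A reader might infer either from halving the degrees of freedom. With equal numbers and pairing unrelated to the data, neither occurs, as the table shows.
- **Arms judged by which one reaches significance.** A reader might infer this from the within-arm reading. The protocol states no such decision rule. How often one arm alone would be significant depends on within-arm power, which the documents do not allow one to set, so no error rate is attached here.
- **The baseline scan is ignored.** The article does not say whether post-treatment or change maps enter the test, and it describes fMRI as reflecting changes.
- **Functional connectivity has no group test.** None is named, but that may be left to the analysis plan. Only the dependence of region selection on the ALFF and ReHo test is raised here.

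**Conclusion.** The concern holds as a stated error. The paired t test named for ALFF and ReHo does not match two independent, unmatched arms. Across arms it is undefined, and within arms it does not compare them. If it is a slip, the wording is wrong. As written, there is no valid between-group test for these primary outcomes, and the region selection for functional connectivity inherits the gap.

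The size lies in the missing or undefined comparison, not in a distorted error rate. The 0.11 chance of equal completer numbers rests on 38 per arm and independent 20% dropout in each arm. The power figures rest on assumed effect sizes. The main conclusion needs neither, since it follows from the design and the sentence alone. It should be settled before the imaging data are analysed.

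**What to change.** Replace the sentence with one pre-specified between-arm test, for example:

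> ALFF and ReHo will each be compared between the arms voxel by voxel, using a general linear model of the post-treatment map with treatment group as factor and the participant's pre-treatment map as covariate. Paired t tests will serve only to describe pre-post change within each arm.

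A two-sample t test of post-minus-pre change, which is the group-by-time interaction, is a valid alternative but not an equivalent one. In post = a + b·group + c·pre, the change-score test fixes c at 1, whereas the model above estimates c. Name only one of them as primary.

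State also that this analysis runs in the imaging software already named, not in SPSS, and confirm that the chosen package accepts a map as covariate. Say that the regions carried into the connectivity analysis come from this between-arm test.

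The cost is a few lines of wording. Both scans are already planned for every patient, so no new data are needed. The article reports that no analysis had been done at the time of writing, so at that point the change could be made without knowledge of results.
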